**Carers:**

- Providing regular informal care to someone living with frailty and MLTCs as defined above for ≥3 months

Informal care includes (but is not limited to) emotional support, prompting with taking medications, getting prescriptions, managing, and organising appointments and care tasks, encouraging participation in social events and physical activity, helping with household tasks, or providing physical care.

People with MLTCs and frailty and their carers may be recruited and involved in the intervention in a dyad, but carer involvement is not required for people with MLTCs and frailty to participate.

## Exclusion criteria

For all participants:

- Unable to provide informed consent
- Unable to communicate in English
- Known contraindications to exercise (as defined by the American College of Sports Medicine)^77^ to include:
  - Unstable cardiac disease (Uncontrolled arrhythmias; unstable angina or heart attack within the last 3 months; persistent uncontrolled hypertension (systolic blood pressure >180 mm Hg or diastolic blood pressure >110 mm Hg); stroke or transient ischaemic attack within the last 3 months)
  - Active infection
  - Significant aortic aneurysm (more than 5.5 cm)
  - Any other condition in which the investigator feel exercise may be contraindicated.
- Current participation in competing clinical trial (as determined by study investigator of this trial).
- Significant cognitive impairment (Mini mental state examination score of less than 24)^78^ or unstable psychiatric disorder that limits active participation in the intervention.
- Serious illness or event with life-expectancy <1year, active malignancy (on chemotherapy/radiotherapy) or other significant illness which, in the opinion of a study clinician, precludes involvement.
- Self-reportedly already regularly engaging in at least 150 minutes of moderate-to-vigorous physical activity per week.

People with MLTCs and frailty:

- Not frail as defined by:
  - eFI:0-0.12 or
  - A CFS score of 1-3 (very fit to managing well).

Carers:

- Providing paid/professional care.

# Trial procedures

This section provides a clear and concise timeline of the trial visits, enrolment process, interventions, and assessments that participants will undertake. These are also summarised in the schedule of procedures outlined below.

## Schedule of procedures

Table 1. Schedule of procedures for the PERSONAL-AGILIY study.

|  | Screening | Consent | Baseline | Week 12 | Week 24 |
| --- | --- | --- | --- | --- | --- |
| Screening* | A |  |  |  |  |
| Consent |  | A |  |  |  |
| Demographic and Medical History# |  |  | A |  |  |
| Body Composition |  |  | A | A | A |
| Blood Pressure |  |  | A | A | A |
| Handgrip Strength |  |  | A | A | A |
| Short Physical Performance Battery (SPPB) |  |  | A | A | A |
| Berg Balance Scale |  |  | A | A | A |
| Physical Activity** |  |  | A | A | A |
| Sedentary Behaviour** |  |  | A | A | A |
| Sleep** |  |  | A | A | A |
| EuroQol-5 Dimensions |  |  | A | A | A |
| Short Form-36 |  |  | A | A | A |
| Late Life Function and Disability Instrument |  |  | A | A | A |
| Patient Outcome Scale |  |  | A | A | A |
| Goal Attainment Scale |  |  | A | A | A |
| Zarit Burden Interview |  |  | C | C | C |
| The 9-item Shared Decision-Making Questionnaire (intervention group only) |  |  |  | A | A |
| The 24-hour Physical Behaviours Burden Questionnaire (intervention group only) |  |  |  | A | A |
| Randomisation*** |  |  | A |  |  |
| Adverse Event Reporting |  |  | A | A | A |
| Interviews |  |  |  |  | A |

A = All participants; P = People with MLTCs and frailty only;C = Carers only.* Screening includes checks for confirmation of eligibility, as described in section 5. #Demographic and medical history includes: sex, date of birth, ethnicity, employment, education, marital status, socio-economic status, and a detailed past medical history including previous or current diseases and surgical interventions will be recorded by the study clinician on the CRF. **Physical activity, sedentary behaviour and sleep will be measured by an accelerometer. Measures include: Device measured steps, MVPA, sedentary behaviour, sleep quality and sleep duration.^***^Randomisation will occur on completion of baseline measures.

## Recruitment

All regulatory approvals, confirmation of capacity and capability and sponsor greenlight will be in place before participants are identified and approached.

### Participant identification

The recruitment phase will commence as soon as all necessary approvals have been received. Potential participants may be identified and/or contacted in the following ways.

### Recruitment from primary and secondary care

Researchers will work closely alongside their local RDN to support recruitment from primary and secondary care, including Participant Identification Centre (PIC) sites. The RDN will support recruitment via their study support service advertising the study and gathering expressions of interest to act as a PIC from sites within LLR. Potential participants will be identified primarily through database searches on clinical systems/electronic health records (I.e., SystmOne). The database search will be completed by people with legitimate access and initially screen for eligible participants based on the criteria outlined in section 5. A study invitation letter with accompanying reply slip/, along with a brief participant information leaflet including a QR code with link to the study website (see section 6.2) will be provided to potentially eligible participants. If no response has been received, a remailing will be conducted. If willing, GP practices will add notes or reminders to medical records within Electronic Health Records to aid recruitment. The study teams will work with the RDN and GP practices to add notes and/or set-up reminders on eligible medical records for a GP or other health care provider to inform them about the trial during routine appointments. In addition, where willing, individual clinicians, GPs and other health care professionals (e.g. practice and clinic staff, social prescribers) may engage in opportunist identification of potentially eligible participants with the provision of study materials and the participant information leaflet.

Recruitment through secondary care will include identification of potentially eligible participants via clinical databases, with subsequent contact as outlined for primary care databases above. The study team will also coordinate with local secondary care services to attend relevant clinics and discuss the study with potential participants who have expressed interest after being told about the study by their health and care providers. Health and care professionals with legitimate access will screen their clinic lists for potentially eligible participants and approach potentially interested and eligible people.

After seeking consent to do so, contact details of interested people identified by health and care practitioners from either primary or secondary care will be shared with the research team, who will then contact the potential participants and share study materials. Whether approached in primary or secondary care, non-clinical members of the research team, or clinical members not involved in the person’s usual care, will not identify participants or access medical records before consent has been obtained. Researchers may however visit clinical sites to promote the study to clinical teams.

### Recruitment through participant and volunteer database

If applicable, participant and volunteer databases within the Leicester Diabetes Centre containing individuals who have consented to be informed of and invited to future research studies may be used. These may be participants that have completed studies previously or volunteers that have not previously been involved in studies but have expressed interest to be considered for future studies.

### Recruitment through community engagement

Participants may be recruited through locally organised relevant community health events. These may consist of having a stand with all the study information and/or presenting the study at these events. Awareness campaigns may also be used as a route to promote the study.

### Recruitment through other methods

The study will be promoted and advertised via several formats including, but not limited to, social media and press releases.  Participant case studies (with media consent in line with UHL Trust policies), which will be used to promote the trial on social media, websites and press releases. Study information, including a brief leaflet about the study, will be distributed by email to various mailing lists held by the University of Leicester NHS Trust and other relevant partner organisations, including but not limited to, local registries, newsletters, Trust members, public and patient involvement/engagement (PPI/E) groups, and Trust staff, local intranets and internal mailing lists.

A range of media may be used to promote the study, including (but not limited to) animations, videos, and QR codes enabling people to access more information. The study team will also distribute posters and information to publicise the study across both clinical (e.g., GP practices, local hospitals, pharmacies) and non-clinical environments (e.g., supermarkets, libraries and community centres), All methods of advertisement will contain the study acronym and logo, a description about the study and contact details of the research team.

### Recruitment procedures

Potential participants identified via primary and secondary care, and those who express interest after seeing local advertising, volunteer database and community engagement will either:

- Be sent a postal or email invitation pack, which will include a letter, participant information sheet, contact details for the research team, and a (where relevant) a reply slip with a pre-paid envelope providing consent for the research site to contact them.

Or

- Scan a QR code which will take them to further information on the study online. A study website containing information about the study will enable potential participants to contact the research team.

Remailing and further follow-up, via email, SMS messaging, phone and other appropriate methods, of non-responders will be considered according to how well recruitment targets are being met.  All potential participants who reply by post or email will be contacted to provide further explanation of the study prior to consent.

### Reimbursement

Participants travel and parking expenses for all visits associated with the study (including those for the interviews undertaken as part of the process evaluation) can be reimbursed.  Participants who are interviewed will be offered a £20 voucher in recognition of their time, and for those interviews which are conducted online, an ‘uplift’ of £5 will be offered. Caring costs will be covered for carers who are interviewed separately in line with current NIHR guidance (up to £15 per hour)^79^.

### Consent

Further information on consent procedures for the interviews can be found in Section 7.5. Participant information sheets, consent forms and any amendments will follow GCP, local regulatory requirements and legal requirements and will have been approved by Research Ethics Committee (REC), Health Research Authority (HRA), Study Sponsor and the local trust R&I department prior to implementation*.*

To allow a wider range of participants to take part should they wish and to ensure that an undue burden is not created, an approach which allows for informed consent to be taken both in-person and remotely via telephone or secure video conferencing (e.g., Zoom or Microsoft Teams) will be used.

Written informed consent will be received after individual discussion between the participant and a member of the research team, with the participant having had sufficient time (at least 24-hours) to consider the participant information sheet, confer with other parties (e.g., family members), and ask any questions related to the study. Written informed consent will be obtained by either by:

- Means of participant dated signature and dated signature of the person who completed consent procedures (for in-person consent)

or

- The researcher will initial the boxes in a bespoke consent form and sign on behalf of the participant (for telephone or online consent).

The person obtaining informed consent will be a suitably trained and competent person who, in the opinion of the Principal Investigator (PI) at each site, will be able to give a full and unbiased explanation of the study (including benefits and risk) to the potential participant. As part of the process, they will make an informed judgement on the person’s capacity to provide informed consent, by checking the participant understands:

- The purpose and nature of the research
- What the research involves, including its potential benefits risks and burdens
- The alternatives to taking part

and that they can:

- Retain the information long enough to make an effective decision
- Make a free choice
- Make this decision at the time it needs to be made.

The person obtaining consent will also have been named in the delegation log of staff as undertaking this duty and approved as study personnel by the relevant governance procedures. Written and audio versions of the participant information sheet and informed consent forms will be presented to the participants detailing no less than: the exact nature of the study; the implications and constraints of the protocol; the known potential risks involved in taking part. It will be clearly stated that the participant is free to withdraw from the study at any time for any reason without prejudice to future care, and with no obligation to give the reason for withdrawal. Participants will also be informed briefly about the process evaluation and be required to consent to being recorded as part of this if required. They will also be required to consent to be contacted about the interviews, although they will not be obliged to take part. A separate consent process will be undertaken for the interview stage (see section 6).

Each participant will be provided with a contact point where they may obtain further information about the trial, a copy of the consent form and participant information sheet. A copy will be placed in their hospital medical records, where possible, and the original copy held in the site master file. A screening log will be designed to identify trends and capture numbers of people screened, eligible, approached, randomised, and numbers accepting their randomised allocation.

The PI will retain overall responsibility for the conduct of the research, including the receipt of informed consent of participants. Where a participant is required to re-consent or new information is required to be provided to a participant it will be the responsibility of the PI to ensure this is done in a timely manner.

## Screening

Screening for eligibility will be performed by an appropriately trained delegated person and will involve telephone, online or in-person screening (according to participant preference) to confirm aspects of the inclusion and exclusion criteria ahead of consent. In-person assessment will take place at the research site, in the participant’s home, or at community locations to increase inclusivity.  Any adverse findings that come to light throughout pre-screening (or at follow-up assessments) will be reported to the participant’s GP. Anonymised information on participants who do not progress beyond each stage of the recruitment and randomisation process will be recorded for CONSORT reporting, including:

- Age
- Sex
- Ethnicity
- The reason they are not eligible for trial participation, or if they are eligible but declined.

A standardised bespoke screening form will be used to check mobility and physical activity exclusion criteria. Potential participants who have been identified as frail via an eFI score or flagged by the adjusted clinical groups (ACG) risk stratification tool at the eligibility phase, or do not have any identified frailty scoring at this stage, will have their frailty status confirmed via CFS score. Cognitive impairment will be screened for at this stage using the MMSE.

## Carer consent

Once eligibility has been confirmed, participants will be asked if they wish to invite a carer to participate with them. Interested carers will be provided with their own brief information leaflet and undertake the consent process outlined within section 6.2.8. Some participants may wish to have a carer present with them during their consent and screening procedures. In these circumstances it may be appropriate to discuss the study with both parties concurrently, and to undertake consent and screening together.

## Baseline data

Prior to randomisation, but after consent, participants will be asked to complete several questionnaires and measures, detailed in section 7. All participants will be asked for consent to access their medical records.

Baseline assessments may be undertaken in any order; although to facilitate complete data collection a preferred assessment order will be established and outlined through the visit case report form. In addition to the measures outlined in section 7, demographics will be collected via a case report form (CRF) completion. For all participants these will include:

- Date of birth (subsequently calculating age)
- Sex
- Gender
- Ethnicity
- Frailty status (CFS) if not already established during screening
- A detailed past medical history including previous or current diseases (subsequently calculating number of long-term conditions)
- Medications

Information on socioeconomic status data collection, informed by relevant NIHR guidance ^80, 81, 82^ will include:

- Living arrangements
- Housing status
- Employment status
- Receipt of benefits
- Level of education attainment
- marital status
- Participant postcode to calculate the index of multiple deprivation (IMD) score

The 3-Item Digital Health Care Literacy Scale will be used to determine participants confidence, familiarity with digital tools and devices^83^. The scale is reliable and validated for use in English speaking populations^83^. This will be undertaken as a one-off measure at baseline, allowing the research team to determine the level of support the participant may need with the digital tools included within the intervention. Participants in the intervention group with low scores (≤ 6) will be supported to access and use the tools as required.

For carers only the following additional information will be collected:

- Relationship to the care recipient
- Length of time in current caring role
- Number of hours of care provided per week
- Caring tasks performed

The baseline visit will occur preferably within 28 days of screening. Baseline assessments will be conducted on a single day as standard but may be conducted across multiple visits where required (e.g., due to participant preference, staff or equipment availability), provided they are completed within a 14-day window.

## Randomisation

Randomisation will occur after baseline assessments. Eligible participants who are living with MLTCs and frailty (and their carer if included) will be randomised in a 2:1 ratio to one of two arms:

- Intervention group: the PERSONAL-AGILITY intervention

OR

- Control group: usual care

The increased ratio of participants within the intervention group will give increased opportunity and exposure to the delivery of the intervention, which will be beneficial to refining and improving it for a future definitive trial.

Stratification will be based on one factor, frailty status, creating two strata (very mild and mild/ moderate and severe). Randomisation and treatment allocation will be performed using a third-party service using variable block sizes of 3 and 6.

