# Trial design

This is a 24-week feasibility randomised controlled trial, with a mixed-methods process evaluation. The trial schematic on page 19 provides an overview of the trial design and core trial visits and process evaluation.

Fifty Individuals aged ≥18 years living with MLTCs and frailty will be enrolled. Participants will be approached via diverse means (including through primary care, secondary care and public advertisement/self-referral), before undergoing eligibility and consent procedures by telephone and/or in-person as required and preferred. Carers will also be invited to take part in the trial as part of a dyad.

Participants will be allocated in a 2:1 ratio in favour of the intervention group, to one of two groups:

- The PERSONAL-AGILITY intervention
- Ongoing USUAL care

Allocation will use stratification based upon frailty status. All participants will undertake three assessments:

- Visit 1 – Week 0 – Baseline Assessments
- Visit 2 – Week 12 – Intermediate Follow-Up Assessments
- Visit 3 – Week 24 – Final Follow-Up Assessments

These visits may be combined where participants take part as a dyad or may be conducted separately if participants prefer.

An embedded mixed methods process evaluation, combining quantitative data (see section 2.3.1) gathered within the trial with observational and qualitative interview data, will provide additional insights into the feasibility and acceptability of both the intervention and the study design. Interviews will be conducted separately to ensure free expression of views and opinions.

The process evaluation will assess the:

- Trials acceptability, including recruitment, procedures and outcomes
- Intervention
  - Implementation: fidelity, dose and reach
  - Potential mechanisms of impact
- Contextual influences.

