### Method of implementing the randomisation/allocation sequence

Allocation will be performed using a validated web-based system (Sealed Envelope Ltd). A letter will be sent to the participant’s GP, notifying them of their patient’s participation in the study and confirming randomisation assignment.

Carers will be randomised as a dyad with the person with MLTCs and frailty. Each participant will be given a unique participant identification (ID) number at randomisation. For people undertaking the intervention with a carer, these ID numbers will be linked.  Participant ID numbers will be used to identify the individual participant throughout the study and will not be re-assigned to any other participant. Due to the nature of the intervention, blinding of the participants and the study team to allocation is not possible. The allocation will be documented within the trial master file and, where possible, participant medical notes.

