## Blinding

It is not possible to blind participants and intervention providers to allocation, due to the nature of the intervention. Furthermore, outcome assessors will not be blinded as this feasibility study does not aim to evaluate intervention effectiveness. Scripts for helping participants who need support to complete PROMs will be developed to minimise response bias.

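### The protocol prints block sizes 3 and 6 for an unblinded team, so about 10% of allocations can be deduced with certainty just before randomisation

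*Protocol*

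**What the plan says.** Protocol section 6.6 (Randomisation) says that people with MLTCs and frailty "will be randomised in a 2:1 ratio to one of two arms". It adds: "Stratification will be based on one factor, frailty status, creating two strata". Allocation is through a third-party service "using variable block sizes of 3 and 6".

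Section 6.6.1 says "Allocation will be performed using a validated web-based system", that "Carers will be randomised as a dyad with the person with MLTCs and frailty", and that "blinding of the participants and the study team to allocation is not possible". Section 6.7 (Blinding) adds that "outcome assessors will not be blinded as this feasibility study does not aim to evaluate intervention effectiveness".

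Section 3 (Trial design) gives the number to be randomised: "Fifty Individuals aged ≥18 years living with MLTCs and frailty will be enrolled". Section 6.3 (Screening) has the Clinical Frailty Scale score confirmed at screening, so the stratum is usually known then; section 6.5 allows scoring at baseline if it has not yet been done. Randomisation follows consent and baseline assessment. Nothing in the protocol restricts who may know the block sizes.

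**The concern.** Central web randomisation conceals the list. It does not conceal what can be worked out from the rules that built the list. Someone who knows the permitted block sizes, the 2:1 ratio and the earlier allocations in a stratum can sometimes deduce the next allocation and can often improve on a guess. Here the sizes are small, there are only two of them, they are printed in a document the study team holds, and the team is not blinded.

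Staff discretion remains before randomisation: when a baseline visit is booked and completed, how actively a carer is invited (section 6.4), and the order in which people ready for randomisation are entered. An expectation about the next arm could influence these steps. What is at stake is mainly the comparability of the arms. Section 2.2 lists potential effectiveness against usual care as a secondary objective, and section 9.5 summarises outcomes by randomised group. The procedures are also meant to inform a definitive trial, so a weakness in concealment could carry over.

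**Working it through.** The protocol gives no predictability figure, so there is nothing to reproduce.

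**Inputs from the protocol.** Block sizes 3 and 6, varied; 2:1 ratio, so a block of 3 holds 2 intervention (I) and 1 control (C) and a block of 6 holds 4 I and 2 C; two frailty strata; 50 allocations, with carers following their dyad.

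**Assumptions.** Each block is size 3 or 6 with probability 0.5 (varied below). The observer knows every earlier allocation in the stratum, but not the size of the current block. Strata are 25/25 (varied below).

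**How certainty arises.** Take the start of a stratum.
- I, I, I, I: every block of 3 contains a control, so this must be a block of 6 with all four intervention places used. The next two are certainly control.
- C, C: a block of 3 has only one control, so this is a block of 6. The next four are certainly intervention.

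**How a good guess arises.** After I, I at the start of a stratum:
- P(I, I | size 3) = 2/3 × 1/2 = 1/3
- P(I, I | size 6) = 4/6 × 3/5 = 2/5
- P(size 3 | I, I) = (1/3) / (1/3 + 2/5) = 5/11
- P(next is C) = 5/11 × 1 + 6/11 × 2/4 = 8/11 = 73%

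Control is then the better guess, but it is not certain.

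**Whole trial.** The same updating was applied after each allocation in 20,000 simulated trials of 50, with strata of 25/25:

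| Quantity | Result |
| --- | --- |
| Allocations certain in advance | 9.5% (about 4.7 of 50) |
| Controls certain in advance | 5.9% (about 1.0 of 16.7) |
| Trials with at least one certain allocation | 92% |
| Trials with at least one certain control | 50% |
| Allocations predictable at 90% or more | 32%, nearly all intervention |
| Controls correctly guessed (P(C) > 0.5) | 34% (about 5.7 of 16.7) |
| Control guesses that are right | 79% |

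**Overall accuracy.** Control guesses per trial = 5.66 / 0.792 = 7.15, of which 7.15 − 5.66 = 1.49 are wrong. The other 50 − 7.15 = 42.85 guesses are intervention, of which 33.34 − 1.49 = 31.85 are right. Total right = 5.66 + 31.85 = 37.51 of 50 = 75.0%. Always guessing intervention is right 33.34 of 50 = 66.7% of the time and identifies no control. The gain is 37.51 − 33.34 = about 4 allocations per trial.

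**Sensitivity.**
- Chance of a block of 3 set to 0.25: 12.4% of allocations and 7.7% of controls certain; a control guess is right 75% of the time.
- Chance of a block of 3 set to 0.75: 5.7% and 3.5% certain; a control guess is right 86% of the time.
- Strata of 15/35 or 10/40: nearly unchanged (9.5% of allocations certain in both).

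**Contrast with one fixed, known size.** The sequences for a block of 3 are CII, ICI and IIC, with 2, 1 and 1 certain places: 4 of 9 = 44.4% of allocations and 1 of 3 controls. For a block of 6 the figures are 28.9% and 20.0%. Mixing the two sizes hides the block boundaries and cuts certainty sharply.

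**The case against.** The best case for the plan has four parts.

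1. The sizes do vary and allocation is through an independent web system. Certainty is therefore far below the fixed-block figures, and accuracy rises only from 67% to 75%. This stands, and it sets the size of the point.

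2. The figures are a ceiling. They assume that the observer knows all earlier allocations in the stratum at the moment of randomisation. That moment comes after consent and baseline, and baseline is preferably within 28 days of screening and may spread over 14 days. At screening or carer invitation, others in the same stratum may still be randomised first. This also stands: a reader might infer that allocations are predictable before enrolment, but the documents do not support that.

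3. The progression criteria in section 9.4 are not comparisons between arms, and the secondary outcomes are descriptive, without p values. Section 6.7 says that effectiveness is not being evaluated. This limits the consequence but does not remove it, because section 2.2 still lists potential effectiveness and section 9.5 still summarises by arm. A reader might extend the argument to retention; that is weak, because everyone knows the arm once it is allocated.

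4. It is tempting to assume a single-centre team that sees everything. The protocol never says single-centre: section 4 describes central coordination, while sections 4, 6.2.8 and 10.4 refer to each site. Since the lists are stratified by frailty only, a coordinating team that sees all allocations could still predict. That any one recruiter sees them all is an inference.

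**Conclusion.** The point holds as a modest weakness in allocation concealment that is cheap to repair. With sizes 3 and 6 equally likely and past allocations known, about 10% of allocations and about 6% of controls can be deduced with certainty just before randomisation (5.7% to 12.4% of allocations and 3.5% to 7.7% of controls over the mixes tried). About a third of controls can be guessed correctly, but roughly one control guess in five is wrong.

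A reader might infer that a third of controls can be foreseen outright. That is true only of fixed blocks of 3, which this protocol does not use; half of the simulated trials contain no certain control. Nor do the 44% and 29% figures describe this design, since they need the current block size to be known.

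The main exposure is the comparability of the arms in the descriptive secondary outcomes, with some scope for influence on booking and carer invitation. The result rests on the assumed size mix and on staff knowing earlier allocations within a stratum. The protocol leaves that knowledge open but does not state it.

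**What to change.** Remove the block sizes from section 6.6 and say only that randomly varied blocks are used, with the sizes held by the third-party service. Have the service set new sizes, in multiples of 3 to keep the 2:1 ratio, recorded only in a restricted document not available to staff who recruit, randomise or assess. New sizes are needed because the present ones are already in print.

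Non-disclosure is the useful part. Wider sizes alone help less. If they were known, sizes 3/6/9 would leave 3.4% of allocations certain and 6/9/12 would leave 2.3%, against 9.5% now. The accuracy of a control guess would fall from 79% to 69% and 63%. The share of controls correctly guessed would stay near 34% to 35%.

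The cost is one sentence in the protocol and a set-up change with the provider. If larger blocks are included, an unfinished last block can leave slightly more imbalance. The largest departure from 2:1 within a stratum is 2s/9 participants for block size s (all 2s/3 intervention places filled first, against 4s/9 expected): 1.3 for size 6, 2.0 for size 9 and 2.7 for size 12.
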